##### Morbidities

3.1.3.2.

The correlation between age at surgery (in number of days of life) and the occurrence of at least one of the elements of post-op morbidity (yes vs. no) will be assessed by describing and comparing age at surgery according to the presence and absence of a morbidity criterion. A comparison test for quantitative data will be used. The Student's t-test will be used if the application conditions are met; otherwise, the non-parametric Mann-Whitney test will be used. This analysis will be conducted with consideration for each element of morbidity in isolation.

##### Length of hospitalization

3.1.3.3.

The correlation between age at surgery (in number of days of life) and the length of postoperative hospitalization will be assessed by estimating the Pearson's correlation coefficient with a 95% confidence interval if the application conditions are met (otherwise, the non-parametric Spearman's correlation coefficient will be estimated with a 95% confidence interval).

##### Moderating role of demographic and surgical factors

3.1.3.4.

The moderating role of demographic characteristics and pre-, intra-, and postoperative factors on the correlation between age at surgery (in number of days of life) and the various prognostic criteria for neonates with complex CHD indicated above will be analyzed using multivariate analyses. For quantitative data (neuropsychological development assessed using Bayley-IV scale scores, neurodevelopment assessed using AIMS scores, and length of postoperative hospitalization), a multivariate linear regression model will be employed. Each of the criteria previously listed will, in turn, be considered a dependent variable. Age at surgery, the explanatory variable of interest, will be systematically incorporated into the models. The main prognostic factors identified in advance according to an analysis of data from the literature, will also be incorporated into the models. Adjusted beta coefficients will be estimated with a 95% confidence interval. Standardized beta coefficients will also be presented to assess the relative role of each factor in the prognosis.

For qualitative data (neurodevelopment judged as normal vs. abnormal in the neuropediatric clinical assessment, the presence of WMIs, the element of morbidity), a multivariate logistics regression model will be utilized. Each of the criteria previously listed will, in turn, be considered a dependent variable. Age at surgery, the explanatory variable of interest, will be systematically incorporated into the models. The main prognostic factors identified in advance according to an analysis of data from the literature will also be incorporated into the models. Adjusted odds ratios will be estimated with a 95% confidence interval. In order to consider the small sample size, the Firth correction may be applied.

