**Methods:**

We hypothesize that earlier surgical timing could represent a neuroprotective strategy that reduces perioperative white matter injuries (WMIs) and postoperative morbidity, leading to improved neurodevelopmental outcomes in infants with complex CHD. Firstly, our prospective study will allow us to determine the correlation between age at the time of surgery (days of life) and neurodevelopmental outcomes at 24 months. We will then analyze the correlation between age at surgery and (i) the incidence of WMIs (through pre- and postoperative MRIs), (ii) postoperative morbidity, and (iii) the duration of the hospital stay.

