For patients with TGA (Transposition of Great Arteries) or HLHS (Hypoplastic Left Heart Syndrome), later cardiac surgery leads to a higher incidence of white matter injuries (WMI) (7, 8), which is a well-known prognostic factor for motor (9–12), language (11), and cognitive (10, 12, 13) impairment, as well as behavioral issues (14). Additionally, Anderson et al. (15) demonstrated that conducting the arterial switch operation (ASO) on neonates with TGA before the third day of life reduced the major postoperative morbidity of these patients in terms of neurological (occurrence of seizures, ischemic stroke), cardiological, and infection complications. Patients with left ventricle hypoplasia operated on later in the neonatal period also presented higher postoperative morbidity (16). Similarly, patients with TGA given the ASO after 2 weeks of life experienced impaired perioperative brain growth and slowed language development (17). Conversely, a major hypotrophy (weight < third percentile) or hemodynamic instability can delay the surgery, which may then be considered too risky. The fetal, pre and intraoperative risk factors of brain injuries are listed in the Table 1. All postoperative morbidities (Table 2) are deemed as potential risk factors for brain injuries.

**Table 1 T1:** Foetal and preoperative risk factors of brain injuries.

	Foetal period	Preoperative period	Intraoperative period
Risk Factors of Brain injuries	Gestational Age	Postnatal diagnosis	CPB duration (min)
	IUGR	Lower arterial oxygen saturation	Aortic clamp time (min)
	Brain volume	Lower apgar scores at 5 min	DHCA (min)
			Selective cerebral perfusion (min)
	Brain immaturity	Abnormal aEEG background pattern	Low Flow
		Longer time to surgery	
		Brain lactates	
		Low flow	
		Male sex	

CPB, Cardiopulmonary bypass; DHCA, Deep hypothermia with circulatory arrest; IUGR, Intrauterine growth restriction; aEEG, amplitude EEG.

**Table 2 T2:** Classification of post-op morbidities.

Morbidity category	Morbidities	
Cardiac / Respiratory	• Cardiac arrest, arrhythmias, JET • Low cardiac output syndrom • Extracorporeal membrane oxygenation • Post-op high-output failure • Re-intubation for acute respiratory distress	• Neonatal necrotizing enterocolitis • Systemic vein thrombosis • Acute renal deficiency with dialysis • Delayed sternal closure • Length of intensive care unit stay
Infectious	• Septicemia, fungemia • Infection of the surgical site, mediastinitis • Endocarditis	• Meningitis • Pneumonia

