### Secondary objectives

1.3.

The secondary objectives of our study are to evaluate the correlation between age at surgery (days of life) of neonates with complex CHD and the following outcomes:
i.the presence and severity of WMIs observed on preoperative and postoperative brain MRI;ii.postoperative morbidity;iii.the duration of the postoperative hospital stay;iv.neurodevelopmental outcomes, including clinical pediatric neurological assessment (4 months, 12 months, and 24 months) and functional motor skill assessment using the Alberta Infant Motor Scale (AIMS; 4 months and 12 months).We will also assess the moderating role of demographic characteristics and pre-, intra-, and postoperative factors on the following outcomes:
i.the frequency of pre-, and postoperative WMIs;ii.postoperative morbidity;iii.neurodevelopmental outcomes, including clinical pediatric neurological assessment (4 months, 12 months, and 24 months), functional motor assessment using the AIMS (4 months and 12 months), and the Bayley-IV test (24 months).

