### Morbidities

2.9.

An analysis will be conducted for postoperative morbidities (see Table 2), including cardiac, hemodynamic, surgical, infectious, and neurological morbidities. Each of these complications will be analyzed independently.

Perioperative demographic and clinical data, including postoperative complications, will be collected retrospectively from prospectively completed medical files. We are particularly interested in the following data:
(i)demographic, including gender, education level, and economic status of the parents;(ii)preoperative, including whether there was a prenatal diagnosis of complex CHD, gestational age at birth, birth weight, head circumference at birth, Apgar score at 5 min, type of complex CHD, whether a Rashkind procedure was performed, the type of ventilation and its duration in days, hypotension requiring treatment, cardiac arrest, and arrhythmia.(iii)intraoperative, including age and weight at the time of surgery, hematocrit in the operating room, type of surgery, CPB time in minutes, selective cerebral perfusion time, and circulatory arrest time in deep hypothermia in minutes.(iv)postoperative, including ventilation (non-invasive, mechanical), duration in days, anesthesia, sedatives and exposure to antiepileptics, medication names and number of days used, and total and postoperative length of their stay in days.

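### Secondary multivariable models assign postoperative factors to the adjusted effect of age at surgery, although the protocol's own hypothesis makes postoperative morbidity a mediator of that effect

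*Protocol article*

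**What the plan says.** The Abstract (Methods) gives the causal hypothesis: earlier surgery "reduces perioperative white matter injuries (WMIs) and postoperative morbidity, leading to improved neurodevelopmental outcomes". The Introduction adds: "All postoperative morbidities (Table 2) are deemed as potential risk factors for brain injuries".

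Section 1.3 sets a secondary objective on the moderating role of demographic, pre-, intra- and postoperative factors. It applies this one set of factors to a list of outcomes that begins with "the frequency of pre-, and postoperative WMIs" and goes on to postoperative morbidity and neurodevelopment.

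Section 3.1.3.4 carries this into the analysis. It covers demographic characteristics and "pre-, intra-, and postoperative factors on the correlation between age at surgery" and the outcomes. On the exposure it says: "Age at surgery, the explanatory variable of interest, will be systematically incorporated into the models". The other covariates are described only as "The main prognostic factors identified in advance according to an analysis of data from the literature". For quantitative outcomes, "Adjusted beta coefficients will be estimated with a 95% confidence interval"; for binary outcomes, adjusted odds ratios are reported in the same way.

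Section 2.9 lists the data collected, among them "postoperative, including ventilation (non-invasive, mechanical), duration in days", sedative and antiepileptic exposure, and total and postoperative length of stay.

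**The concern.** A covariate that lies between exposure and outcome differs from a confounder. Adjusting for a confounder removes bias from the timing effect. Adjusting for a mediator removes part of the effect itself. Section 3.1.3.4 selects covariates because they are prognostic and sets no rule on whether they come before or after the exposure, or before or after the outcome.

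This matters because these are the only analyses described that adjust for anything. The main analysis and the comparisons in 3.1.3.1 to 3.1.3.3 are unadjusted, while the Introduction acknowledges that very low weight or haemodynamic instability can postpone the operation. A reader who wants a confounder-adjusted estimate of timing will therefore turn to 3.1.3.4. The Conclusion intends the results to feed timing guidelines and a later interventional study. A small adjusted coefficient could be taken to mean that timing matters little, when the model had conditioned on the mechanism by which timing is supposed to act.

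**Working it through.** The plan gives no figure on this point to reproduce. The main check is of order in time and causal role; the arithmetic only illustrates scale.

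**1. Role of the postoperative factors.** The Abstract and Introduction together give this chain: age at surgery → perioperative white matter injury (WMI) and postoperative morbidity → neurodevelopment. Postoperative complications sit in the middle. Ventilation days, sedation and stay (2.9) accompany them. Under the protocol's hypothesis these are mediators.

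**2. Moderation, mediation or adjustment.** A moderator changes the size of the timing effect and is tested with a product term (age × factor). A mediator carries the effect and needs a mediation analysis. Section 3.1.3.4 describes neither. It describes age plus other factors, with adjusted and standardised coefficients. A main-effects model of that kind cannot show moderation.

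**3. Order in time for preoperative WMI.** Section 2.6 places the preoperative MRI immediately before the operation. Section 3.1.3.1 analyses both the preoperative and the postoperative MRI. Section 1.3 applies intra- and postoperative factors to both. Bypass time or postoperative ventilation cannot affect a lesion already imaged before surgery. This step needs no assumption.

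**4. Same variable in two roles.** Postoperative length of stay is a collected postoperative factor (2.9) and a dependent variable (3.1.3.4). Table 2 also counts length of intensive care stay as a morbidity.

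**5. Illustration of size.** Take a linear path model with standardised variables:

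- total effect c = c′ + a·b, where a is age → mediator, b is mediator → outcome and c′ is the direct effect;
- adjusting for the mediator returns c′ = c·(1 − share mediated);
- partial correlation = (c − r_ym·a) / √[(1 − r_ym²)(1 − a²)], with r_ym = b + a·c′;
- approximate power = Φ(|atanh r|·√(n − 3) − 1.96) unadjusted, with √(n − 4) for one covariate.

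Inputs: n = 100 and two-sided 5% alpha (3.1.1). Two totals are used: 0.39, which 3.1.1 states for the whole cohort, and 0.28, which its inputs give: tanh((1.960 + 0.842)/√97) = 0.28. That discrepancy is a separate matter. The negative sign follows the hypothesis. The shares and a are assumptions; the documents give none.

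Worked case: c = -0.28, share 50%, a = 0.5. Then c′ = -0.14, b = -0.14/0.5 = -0.28 and r_ym = -0.28 + 0.5·(-0.14) = -0.35. Partial r = (-0.28 + 0.175)/√(0.8775·0.75) = -0.105/0.811 = -0.129. Power = Φ(0.130·√96 − 1.96) = 0.25, against 0.81 unadjusted.

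| Total r | Unadjusted power | Share mediated | Adjusted beta | Power, a = 0.3 | Power, a = 0.5 |
|---|---|---|---|---|---|
| -0.28 | 0.81 | 25% | -0.21 | 0.55 | 0.46 |
| -0.28 | 0.81 | 50% | -0.14 | 0.33 | 0.25 |
| -0.28 | 0.81 | 75% | -0.07 | 0.16 | 0.10 |
| -0.39 | 0.98 | 25% | -0.29 | 0.87 | 0.77 |
| -0.39 | 0.98 | 50% | -0.20 | 0.75 | 0.48 |
| -0.39 | 0.98 | 75% | -0.10 | not possible | 0.19 |

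(Not possible: those paths would explain more than all of the outcome variance.)

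**6. Direction.** The table assumes that the mediator and the outcome share no unmeasured cause. If disease severity drives both postoperative complications and neurodevelopment, conditioning on complications links age to severity. This can push the coefficient either way.

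**The case against.** The strongest reply is that the article does not list the final covariates. Section 2.9 is a data-collection list, not a model specification, and Table 1 groups brain-injury risk factors under foetal, preoperative and intraoperative headings only. A reader might infer that ventilation days, sedation or complications will certainly be entered beside age at surgery. The documents do not support that, and an article may leave the list to a fuller plan. What remains is that 1.3 and 3.1.3.4 expressly assign postoperative factors to these models. That is a stated choice of scope, not a missing detail.

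Second, 3.1.3.4 is partly prognostic: standardised coefficients are meant to compare the weight of each factor. This is fair, and a prognostic model may contain postoperative factors. But the same section names age at surgery as the variable of interest, and one model is made to serve both purposes.

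Third, 1.3 gives one collective list of factors and one of outcomes, and need not mean that every factor enters every model. This is why the preoperative WMI point concerns the wording rather than a specified model. The same holds for length of stay: nothing says it will be used to predict itself.

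Fourth, a reader might infer that the main result is compromised, or that bias must run toward zero. Neither follows. The main analysis (3.1.2) is an unadjusted correlation, and collider bias has no fixed direction.

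**Conclusion.** The point holds as a should-fix defect in a secondary analysis. Sections 1.3 and 3.1.3.4 assign postoperative factors to models that report an adjusted effect of age at surgery, label them moderators, and state no method that would show moderation or mediation. If they are entered, the coefficient is not the total effect of timing. As worded, 1.3 also breaks time order for preoperative WMI, and length of stay appears in two roles.

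The amount of effect lost cannot be stated. The illustrated loss of 25% to 75% of the coefficient, and the matching fall in power, rest on assumed paths, a single mediator and no unmeasured common cause. The loss of the mediated part also assumes that the protocol's hypothesised pathway is right. The time-order point on preoperative WMI rests on none of these assumptions.

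**What to change.** Reword 1.3 and 3.1.3.4 along these lines:

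- **Models estimating the effect of age at surgery:** adjust only for factors that precede the waiting period, namely demographics, CHD class, prenatal diagnosis, gestational age, birth weight, Apgar score, and status at birth or admission. Being recorded before surgery is not enough.
- **Preoperative variables that can accrue while waiting** (such as ventilation days, hypotension and cardiac arrest): use them in a sensitivity analysis. They may delay surgery and so confound, or result from delay and so mediate.
- **True moderators:** test with an age × factor interaction term.
- **Intra- and postoperative factors:** put them in a separately labelled mediation or prognostic model that excludes any component of the outcome being modelled. Length of stay, for example, should not appear on both sides.
- **Preoperative WMI:** allow only factors that precede the preoperative MRI.

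The change is to analysis wording and needs no new data. The cost is one additional labelled model, plus the sensitivity analysis.

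### The moderation analysis lists models with no age-by-factor term, so as listed they give adjusted associations and cannot show whether the effect of surgical timing varies by factor

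*Protocol article*

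**What the plan says.** The objective is worded in two ways.

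- Section 1.3 (Secondary objectives): "We will also assess the moderating role of demographic characteristics and pre-, intra-, and postoperative factors on the following outcomes". The list that follows names white matter injury, postoperative morbidity and neurodevelopment.
- Section 3.1.3.4 (Moderating role of demographic and surgical factors): "The moderating role of demographic characteristics and pre-, intra-, and postoperative factors on the correlation between age at surgery" and the prognostic criteria is to be analysed by multivariate models.

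Section 3.1.3.4 then fixes what goes into the models and what comes out.

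- Terms: "Age at surgery, the explanatory variable of interest, will be systematically incorporated into the models", and "The main prognostic factors identified in advance according to an analysis of data from the literature, will also be incorporated into the models".
- Output for continuous outcomes: "Adjusted beta coefficients will be estimated with a 95% confidence interval".
- Output for binary outcomes: "Adjusted odds ratios will be estimated with a 95% confidence interval".
- Interpretation in the linear models: "Standardized beta coefficients will also be presented to assess the relative role of each factor in the prognosis".

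The only stratified analysis is in section 3.1.2 (Main analysis), where the correlation with age at surgery is estimated for the whole cohort and again within each type of CHD. No comparison between types is named.

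**The concern.** A factor that moderates the correlation between age at surgery and an outcome is an effect modifier: the age slope, or the age odds ratio, differs across its levels. That is estimated by a product of age and the factor, or by an explicit comparison of slopes. A model with age and the factor as separate terms forces one age effect on everyone. Its coefficient for the factor says how the outcome differs by factor at a given age, which is a different question.

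The study wants a timing cut-off for each CHD type and hopes to inform guidelines (Introduction and Conclusion). Whether timing matters more in some infants than in others is therefore close to its purpose. If section 3.1.3.4 is followed as listed, the analysis under the moderation heading carries no information on that.

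**Working it through.** **1. Aim against model.** The opening sentence of section 3.1.3.4 concerns a change in the age-outcome correlation. The listed linear model is

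outcome = b0 + b1·age + b2·factor + … + error.

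The age slope is b1 at every level of every factor. The logistic models likewise have one age odds ratio. Moderation needs an added b3·age·factor, and b3 is the quantity of interest. No product term, interaction test or comparison of slopes is named anywhere in the article.

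**2. What the listed model returns.** With two equal groups and the same age spread in each, the common slope is the mean of the two group slopes. Using the Bayley-IV SD of 15 given in section 2.8.2:

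- Correlations -0.5 and 0.0: slopes 15 × (-0.5) = -7.5 and 0, mean -3.75 points per SD of age.
- Uniform correlation -0.25: slope 15 × (-0.25) = -3.75.

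A simulation (4,000 runs, n = 100, assumed 50/50 binary factor, standard-normal age, no dropout) agrees:

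| True correlations in the two halves | Age slope, listed model | Factor significant, listed model | Product term significant when added |
|---|---|---|---|
| -0.5 and 0.0 | -3.73 | 4.8% | 73% |
| -0.25 and -0.25 | -3.76 | 4.9% | 5% |
| -0.5 and +0.5 | about 0 | 4.5% | about 100% |

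On these coefficients the first two rows cannot be told apart. This follows from the form of the model and is not evidence about this cohort.

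**3. What an interaction term could detect.** The plan gives no power figure for moderation, so there is none to reproduce. Its whole-cohort figure of r = 0.39 at n = 100 is a separate matter and is not used here.

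Assume a residual SD of 14, the same age spread in each group and complete follow-up. For a slope difference d per SD of age between groups of n1 and n2:

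SE = 14 × √(1/n1 + 1/n2), power ≈ Φ(d/SE − 1.96).

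For two groups of 50, SE = 14 × √0.04 = 2.80. For d = 4, 4/2.80 = 1.43 and Φ(−0.53) = 30%. The class sizes are those planned in section 3.1.1 (50, 15, 10 and 25).

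| Comparison | SE | d = 4 | d = 6 | d = 8 |
|---|---|---|---|---|
| Balanced binary factor, 50 vs 50 | 2.80 | 30% | 57% | 81% |
| Class I vs IV, 50 vs 25 | 3.43 | 21% | 42% | 65% |
| Class I vs II, 50 vs 15 | 4.12 | 16% | 31% | 49% |
| Class I vs III, 50 vs 10 | 4.85 | 13% | 24% | 38% |

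The approximation runs slightly high. A simulation of the balanced case (3,000 runs) gave 28, 54 and 79%.

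**4. The by-type correlations.** Comparing two correlations at 80% power and two-sided 5% needs a Fisher z difference of (1.960 + 0.842) × √(1/(n1−3) + 1/(n2−3)). Class I vs IV gives 2.802 × √(1/47 + 1/22) = 0.72, for example r = 0 against 0.62. Class I vs III gives 2.802 × √(1/47 + 1/7) = 1.14, for example 0 against 0.81. Reading the separate correlations side by side is therefore a weak guide to whether they differ.

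**The case against.** Four points can be made for the plan.

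- **The objective may not mean effect modification.** Section 1.3 has the factors acting on the outcomes. If moderating there means prognostic, adjusted betas and odds ratios answer it. This stands. A reader might infer that a stated secondary objective gets no answer at all, and the wording of section 1.3 does not support that. It does not rescue section 3.1.3.4, whose own opening sentence is about the age-outcome correlation.
- **Interactions are not excluded, and an article condenses a fuller document.** It is true that main effects only is an inference from the terms listed. But the article does not leave the method open. It names the models, their terms, their outputs and, for the linear models, their reading, and these fit a prognostic question. That is a mismatch within the text and not a missing detail.
- **CHD type is partly covered.** Section 3.1.2 gives correlations with 95% confidence intervals by type, and the Limitation section accepts that an optimum may be definable only for frequent types. This stands as description. No test that the types differ is named, and the other factors have no stratified analysis.
- **Misreporting is not shown.** A reader might infer that covariates will be published as moderators. The plan says the standardized coefficients show relative roles in prognosis, which suits main effects, so that inference is speculative.

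**Conclusion.** The point holds in a limited form. Section 3.1.3.4 states a moderation aim, and the models it lists estimate adjusted associations with one common age effect. Followed as listed, they cannot show whether that effect varies by factor. Sections 1.3 and 3.1.3.4 differ on what the objective is, and the by-type correlations in section 3.1.2 describe one candidate moderator without testing it.

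The primary estimate, the sample size and the conduct of the study do not depend on this. The mismatch itself needs no numerical assumption. The power figures rest on a residual SD of 14, equal age spread across groups and no dropout, none of which the article gives. Equal age spread is doubtful for Clancy class, since the Introduction describes a ten-day window for TGA and more variable timing for HLHS. The roughly 30, 55 and 80% for a balanced binary factor is too favourable for Clancy class: about 20, 40 and 65% for class I versus IV, and lower for classes II and III.

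**What to change.** - Reconcile sections 1.3 and 3.1.3.4 so that both state the same objective.
- Label the existing models as adjusted association or prognostic-factor analysis.
- If moderation is intended, add age-by-factor interaction terms for a short list of preoperative factors named in advance. Include Clancy class, with sparse classes combined if needed; prenatal diagnosis and parental education are possible others among the data already collected. Preoperative factors are preferable because the study itself hypothesizes that timing affects postoperative morbidity, so later factors may be consequences of age at surgery.
- Report each interaction with its 95% confidence interval and label the set exploratory.

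The cost is some rewording and a few model terms, with no new data or patients. The drawback is imprecision at n = 100: a non-significant interaction could not be read as evidence that timing matters equally in all infants.
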